## INTERVENTIONS

|                              |                                                                                                                                                                                                                                                                                                                                                                                                 |
|------------------------------|-------------------------------------------------------------------------------------------------------------------------------------------------------------------------------------------------------------------------------------------------------------------------------------------------------------------------------------------------------------------------------------------------|
| Treatment             | 
Patients will be randomized 1: 1 to receive one of the following treatments
 
 
– Arm A (Intervention): Standard therapy with COVID-19 Convalescent Plasma (CCP). Patients in this arm receive three consecutive doses (200 ml/day for 3 days) of ABO matched CCP.
 
– Arm B. (Control): Standard therapy with no CCP
 
 |
| Stopping rule         | 
The study will be discontinued if 6 (10%) trial participants in the arm A will have a severe adverse event connected with plasma infusion (Appendix B).
                                                                                                                                                                                                                                  |
| Concomitant therapies | 
Patients enrolled in this study receive standard therapies in addition to CCP. The enrollment of participants in other interventional trials is not allowed.
                                                                                                                                                                                                                             |

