| Trial design  | This is a randomized phase II/III study designed to evaluate the efficacy of convalescent plasma, when used in combination with standard therapy to prevent the progression of pneumonia in elderly COVID-19 patients with comorbidities. The trial will start with a screening Phase II trial designed with two-tailed $\alpha=0.2$ . In case of positive result the trial will proceed in a formally comparative phase III trial ( $\alpha=0.05$ ). Three studies have so far reported the use of CCP in ventilated patients without recording adverse events, but data on patients in earlier phase of disease are lacking. For this reason, the first 57 patients will be observed in order to assess preliminarily the safety of CCP in this population. |
| Study setting | Participating centers are: 

– Fondazione Policlinico Gemelli IRCCS (coordinating center)

– Istituto Nazionale Malattie Infettive Lazzaro Spallanzani IRCCS

– Ospedale SS Annunziata, Chieti

                                                                                                                                                                                                                                                                                                                                                                                                                                                                                                    |

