**Sample size**

**Phase II.** To demonstrate that adding CCP to standard therapy is associated with an increase of proportion of patients without progression from 20% (control, Arm B) to 40% (treatment, Arm A), with a 80% power and a two-tailed alpha error of 0.2, 114 (57 per arm) evaluable patients are needed, with an OR for treatment of 0.375.

**Phase III.** To demonstrate that adding CCP to standard therapy is associated with a reduction of the proportion of patients progressing to severe pneumonia from 40% (control, Arm B) to 20% (treatment, Arm A), with a 80% power and a two-tailed alpha error of 0.05, 182 (91 per arm) evaluable patients are needed, with an OR for treatment of 0.375.

Chow, SC, Shao J and Wang H. 2003. Sample Size Calculations in Clinical Research. Marcel Dekker. New York.

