## **METHODS: ASSIGNMENT OF INTERVENTIONS**

### **Allocation and sequence generation**

Treatment allocation will be randomized between arms A and B with a ratio 1:1 and will be the same in phase II and phase III. Randomization sequences will be generated at Fondazione Policlinico Gemelli IRCCS.R through the RedCap web application, uploading the allocation table through the randomization module (ref: <https://www.project-redcap.org/>).

Randomized stratification will be performed according to age (under/over 80 years), and sex.

**Blinding (masking)** The assignment to intervention will be unmasked to all trial participants (care providers, outcome assessors, and data analysts)

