Unexpected' adverse reaction - Definition: Article 2(p) of Directive 2001/20/EC defines 'unexpected adverse reaction' as follows: 'an adverse reaction, the nature or severity of which is not consistent with the applicable product information (e.g. investigator's brochure for an unauthorised investigational product or summary of product characteristics for an authorised product)'.

The term 'severity' is used here to describe the intensity of a specific event. This has to be distinguished from the term 'serious'. Reports which add significant information on the specificity, increase of occurrence, or severity of a known, already documented serious adverse reaction constitute unexpected events

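### The safety stopping rule's count (6) and percentage (10%) agree only with the Phase II plasma arm, yet the rule is written for the whole Phase II/III study

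*Protocol*

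**What the plan says.** The stopping rule in the Protocol's Interventions table is one sentence: "The study will be discontinued if 6 (10%) trial participants in the arm A will have a severe adverse event connected with plasma infusion", with a pointer to Appendix B. It does not say what the 10% is a percentage of, when it is assessed, or in which phase.

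The Trial design entry describes a single Phase II/III study. Because data on plasma in earlier disease are lacking, it adds that "the first 57 patients will be observed in order to assess preliminarily the safety of CCP in this population".

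The Sample size section gives the arm sizes. For Phase II, "114 (57 per arm) evaluable patients are needed"; for Phase III, "182 (91 per arm) evaluable patients are needed". On allocation: "Treatment allocation will be randomized between arms A and B with a ratio 1:1 and will be the same in phase II and phase III".

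Appendix B carries *severe* in its title, but the category it defines is *serious* adverse events. In explaining unexpected reactions it says that severity is "used here to describe the intensity of a specific event. This has to be distinguished from the term" *serious*.

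**The concern.** A count and a percentage can stand for the same threshold only at one denominator. Here the denominator is left out, and the rule applies to a study whose plasma arm has two planned sizes. A rule that is consistent in Phase II therefore becomes two different rules in Phase III, and whoever applies it must choose between them with the events already in view, in an open-label trial.

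The number 57 raises a linked question. It is the Phase II size per arm, but the safety look applies it to patients without naming an arm. Whether the look holds 57 plasma recipients or about half that number changes how much it can show about safety.

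This is the only explicit safety stopping rule in the document, so the reading chosen decides whether the trial continues.

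**Working it through.** **Inputs.** Threshold: 6 arm A participants, labelled 10% (Interventions). Arm sizes: 57 in Phase II and 91 in Phase III (Sample size). Allocation: 1:1 in both phases (Allocation and sequence generation). The total of 148 = 57 + 91 is an assumption: the Protocol does not say whether the 91 are all new patients or whether events carry over between phases.

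**Arm sizes reproduced.** For 20% against 40%, the standard two-proportion formula with continuity correction gives:
- Phase II ("with a 80% power and a two-tailed alpha error of 0.2"): 56 per arm, against 57 stated.
- Phase III ("with a 80% power and a two-tailed alpha error of 0.05"): 91 per arm, as stated.

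So 57 and 91 are genuine per-arm sizes and the right denominators to test.

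**Where the 10% comes from.** 6/57 = 10.5%, and 10% of 57 = 5.7, which rounds up to 6. The match is approximate: 6 is exactly 10% of 60, and 10% rounded up gives 6 for any arm size from 51 to 60. Of the planned arm sizes, only 57 lies in that range.

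**The two halves of the rule at each denominator.**

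| Arm A patients | 6 as a share | 10% of the arm | Fewest participants reaching 10% |
|---|---|---|---|
| 57 | 6/57 = 10.5% | 5.7 | 6 |
| 91 | 6/91 = 6.6% | 9.1 | 10 (9/91 = 9.9%) |
| 148 (assumed) | 6/148 = 4.1% | 14.8 | 15 |

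In a Phase III arm of 91, any total from 6 to 9 meets the count and falls short of the percentage.

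**Chance of reaching the threshold.** With *n* plasma patients and true rate *p*, P(X ≥ 6) = 1 − Σ C(n,k) pᵏ(1−p)ⁿ⁻ᵏ, summed over k = 0 to 5. The rates are illustrative.

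| True rate | n = 57 | n = 91 | n = 148 |
|---|---|---|---|
| 1% | below 0.1% | 0.03% | 0.4% |
| 2% | 0.1% | 1.0% | 7.8% |
| 3% | 0.7% | 5.6% | 28.5% |
| 5% | 6.5% | 30.4% | 75.4% |
| 6% | 12.6% | 46.7% | 88.4% |
| 10% | 51.1% | 90.2% | 99.8% |

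If the rule in Phase III is instead the percentage, assessed on the full arm of 91, the same formula with a threshold of 10 gives P(X ≥ 10) = 1.6% at a true rate of 5%, against 30.4% for the count.

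**The safety look.** Under 1:1 allocation, 57 randomised patients contain about 57/2 = 28.5 plasma recipients, so 28 or 29. If no events are seen, the one-sided 95% upper limit is 1 − 0.05^(1/n): 10.1% for 28, 9.8% for 29 and 5.1% for 57. The chance of seeing at least one event at a true rate of 5% is 1 − 0.95ⁿ: 76% for 28 and 95% for 57.

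**The case against.** The best defence is that the three figures fit together if the authors had the Phase II plasma arm in mind throughout: 57 recipients, a look at those 57, and 6 of 57 as roughly 10%. On that reading the safety look is complete. This stands as a plausible intention, so the look is an ambiguity. A reader might infer that it would hold only about 28 recipients, but that is just the literal reading. Nor can one infer that the look fails to exclude 10%: with no events the limit is 10.1% for 28 recipients and 9.8% for 29, and the Protocol calls the look preliminary without setting such a target.

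A reader might also infer that the trial would probably stop in Phase III at rates well below 10%. The figures do not support that for 91 patients: the chance is 5.6%, 30% and 47% at true rates of 3%, 5% and 6%, and it passes one half only near 6.25%. A better-than-even chance at 5% needs the cumulative 148. At 1% or 2% the chance is small on either denominator. The Protocol's 1 in 100 figures for allergic or febrile reactions and for circulatory overload (Benefit/risk assessment) cannot settle which rate applies, because they carry no severity and no per-transfusion or per-patient unit.

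The gap between *severe* and *serious* is mainly terminology. The title of Appendix B and the Phase III outcome list both use *severe*, the latter with the abbreviation SAE, so the intended referent can be guessed.

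Finally, a fixed count of 6 is workable as a ceiling, and the primary analysis does not depend on it. That is true, but the sentence also states 10%, and nothing says which figure governs once they part.

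**Conclusion.** The point holds as an internal contradiction in a decision threshold. In Phase II the count and the percentage agree to within rounding. In a Phase III arm of 91 they differ by 4 participants (6 against 10), and totals of 6 to 9 give opposite decisions. At an illustrative true rate of 5%, the chance of reaching 6 runs from 6.5% (57) through 30% (91) to 75% (148), depending only on a denominator that the Protocol leaves open.

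This rests on the rule carrying into Phase III. The wording supports that, since the rule discontinues the study and the study is defined as Phase II/III, but the Protocol does not say so outright. The 148 further assumes that the phases are counted together.

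The safety look is a second, smaller ambiguity: 57 randomised patients (about 28 to 29 recipients) or 57 recipients. No view is taken on what threshold is right.

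**What to change.** Reconcile the Stopping rule, Trial design and Sample size entries in one amendment:

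- State whether the rule is a count or a proportion, its arm A denominator (for example, participants transfused so far) and the phases it covers, including whether Phase II events carry forward.
- If it is a count, delete the 10% or give the percentages it implies for each arm size. If it is a proportion, give the matching count at each assessment.
- State the safety look in plasma recipients, if that is what is meant.
- Use one event term in the rule, aligned with the serious adverse event definition in Appendix B.

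The choice of threshold is left to the sponsor's clinicians. The cost is a few lines of wording, with a short table of stopping probabilities if wanted, and no extra patients.

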## OUTCOMES AND ENDPOINTS

|                 |                                                                                                                                                                                                                                                                                                                                                                                                                                                                                    |
|-----------------|------------------------------------------------------------------------------------------------------------------------------------------------------------------------------------------------------------------------------------------------------------------------------------------------------------------------------------------------------------------------------------------------------------------------------------------------------------------------------------|
| Phase II | 
Primary outcome
 
 
– Proportion of patients without progression in severity of pulmonary disease defined as worsening of 2 points in the ordinal scale of WHO within day 14.
 
 
The WHO ordinal scale to assess the disease progression is provided in Appendix C.
 
Secondary outcome
 
 
– Decreased viral load on nasopharyngeal swab (days 6 and 9)
 
 |
|-----------------|------------------------------------------------------------------------------------------------------------------------------------------------------------------------------------------------------------------------------------------------------------------------------------------------------------------------------------------------------------------------------------------------------------------------------------------------------------------------------------|

## Phase III

Phase III of the study will start soon after completing the analysis of data relative to phase II and if the primary outcome of phase II is met.

### Primary outcome

- Proportion of patients without progression in severity of pulmonary disease defined as worsening of 2 points in the ordinal scale of WHO within day 14.

### Secondary outcomes

- Decreased viral load on nasopharyngeal swab (days 6, 9 and 14)
- Decreased viremia at day 6 and 9
- Increased antibody titre against SARS-CoV2 (days 30 and 60)
- Proportion of patients with negative of SARS-CoV2 nasopharyngeal swab (day 60)
- Length of hospital stay
- Mortality rate at day 28
- Total plasma related adverse event (Febrile reactions, TRALI, TACO, TTI) (day 60)
- Total non-plasma related adverse events (day 60)
- Severe adverse events (SAE) (day 60)

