| Phase III endpoints | 
Primary
 
 
– Proportion of patients without progression at day 14
 
 
Secondary
 
 
– Viral load on nasopharyngeal swab at days 6,9 and 14
 
– Viremia at days 6 and 9
 
– Antibody titer against SARS-CoV2 at days 30 and 60
 
– Proportion of patients with negative of SARS-CoV2 nasopharyngeal swab at day 30
 
                                                |
| Study population    | Adult patients with confirmed COVID-19                                                                                                                                                                                                                                                                                                                                                                                                                                                                     |
| Inclusion criteria  | 
Inclusion criteria are all the following:
 
 
– Age <math>\geq 65</math>
 
– evidence of pneumonia by CT scan
 
– <math>\text{PaO}_2/\text{FiO}_2 \geq 300</math> mmHg
 
– Presence of one or more comorbidities (list provided in annex 1)
 
– Signed informed consent
 
                                                                                                                                            |
| Exclusion criteria  | 
Exclusion criteria include one of the followings:
 
 
– severe COVID-19 disease
 
– <math>\text{PaO}_2/\text{FiO}_2 < 300</math> mmHg
 
– impending cardiopulmonary arrest
 
– refusal to blood product transfusions
 
– severe IgA deficiency
 
– any life-threatening comorbidity or any other medical condition which, in the opinion of the investigator, makes the patient unsuitable for inclusion
 
 |

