#### Screening phase: day -1

#### Baseline visit: day 0:

Physical examination and vital signs (blood pressure, heart rate, respiratory rate, temperature), Respiratory status (pO2/FiO2 and SpO2 at rest if applicable), ECG; blood sampling for ABO groups (on two separate samples), RT-PCR for SARS-CoV-2 on nasopharyngeal swab. routine blood tests (blood count, creatinine, BUN, sodium, potassium, ALT, AST, LDH, fibrinogen, D-dimer, ferritin, CRP), viremia, anti SARS-Cov-2 antibody screening, IL6.

**Plasma administration: days 1,2, 3.** All patients will sign the informed consent to receive blood products in use at each center.

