**Daily study assessment: days 1 to 14**

Physical examination and vital signs (blood pressure, heart rate, respiratory rate, temperature, oxygen supplementation), Respiratory status (pO2/FiO2 and SpO2 at rest if applicable), ECG and chest scan (on day 7 and 14, or additional days if clinically advised); routine blood tests (blood count, creatinine, BUN, sodium, potassium, ALT, AST, LDH, fibrinogen, D-dimers, ferritin, CRP, every three days unless clinically advised), RT-PCR SARS-Cov2 on rhino-pharyngeal swab at the same time points of routine blood tests until 2 consecutive negative swabs within 24 hours, viremia (day 6, day 9, day 12 and day 14), anti SARS-Cov-2 antibody screening (day 14), IL6 (day 3, day 6, day 9).

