**Day 60 visit**

physical examination and vital signs and data on respiratory status and oxygen supplementation, anti SARS-Cov-2 antibody screening.

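### Phase III swab negativity is set at day 30 in one place and day 60 in another, the written visits list no swab on either day, and the three-day swab interval does not secure the day-14 viral load

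*Protocol*

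**What the plan says.** **Swab negativity (Phase III secondary).** The Study Synopsis has "Proportion of patients with negative of SARS-CoV2 nasopharyngeal swab at day 30". The Secondary outcomes list under Outcomes and Endpoints has "Proportion of patients with negative of SARS-CoV2 nasopharyngeal swab (day 60".

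**Late visits.** The Day 60 visit consists of "physical examination and vital signs and data on respiratory status and oxygen supplementation, anti SARS-Cov-2 antibody screening", and the Day 30 visit has the same list.

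**When swabs are taken.** The baseline visit on day 0 includes "RT-PCR for SARS-CoV-2 on nasopharyngeal swab". After that, swabs appear only under "Daily study assessment: days 1 to 14", as "RT-PCR SARS-Cov2 on rhino-pharyngeal swab at the same time points of routine blood tests until 2 consecutive negative swabs within 24 hours". The routine bloods that set this timing are done "every three days unless clinically advised".

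**Swab viral load.** The synopsis uses days 6, 9 and 14 in both phases, and so does the Phase III list in the body. The Phase II list in the body has "Decreased viral load on nasopharyngeal swab (days 6 and 9", without day 14.

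**The concern.** An analysis plan can say how an endpoint is analysed, but it cannot recover a swab that was never taken. The protocol therefore has to be right about which day is measured and at which visit the sample is collected. Here the endpoint list and the visit list disagree.

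If sites follow the written visits, any swab at day 30 or 60 would be one taken for clinical reasons. It would come from a selected subset of patients, in a trial where care providers know the allocation. The viral-load endpoint matters too. Reducing viral load is a stated objective, and the Rationale treats viral load in blood and swab as the evidence that plasma acts on the infection.

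**Working it through.** The plan has no figure to reproduce here. The check compares endpoint days with sampling days.

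**Step 1: swab negativity at day 30 or 60.**

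| Source | Day 30 | Day 60 |
|---|---|---|
| Synopsis, Phase III endpoints | endpoint day | not named |
| Body, Phase III secondary outcomes | not named | endpoint day |
| Written visit list: antibody test | yes | yes |
| Written visit list: swab or RT-PCR | no | no |

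Antibody titre is an endpoint at days 30 and 60, and its test is listed at both visits. So the visit lists do name the laboratory tests that endpoints need, and the missing swab is not merely a matter of short lists.

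**Step 2: can a three-day swab grid serve days 6, 9 and 14?** A three-day grid contains two days only if the gap between them is a multiple of 3.

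- 9 − 6 = 3, a multiple of 3.
- 14 − 9 = 5, not a multiple of 3.
- 14 − 6 = 8, not a multiple of 3.

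All possible grids up to day 14:

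| Start | Grid | Day 6 | Day 9 | Day 14 |
|---|---|---|---|---|
| Day 0 | 0, 3, 6, 9, 12 | yes | yes | no |
| Day 1 | 1, 4, 7, 10, 13 | no | no | no |
| Day 2 | 2, 5, 8, 11, 14 | no | no | yes |

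The grid that serves days 6 and 9 ends at day 12; its next point would be day 15, outside the window. The same section lists viremia on days 6, 9, 12 and 14, and names day 14 for antibody and chest scan as well. Day 14 was added by name for those tests but not for the swab.

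**Step 3: effect of the swab stopping rule.** Swabbing ends after two consecutive negatives. If, for example, swabs on days 3 and 6 are accepted as those two negatives, the patient has no further scheduled swab on day 9 or 14. The viral loads observed on those days then come only from patients who have not cleared, a group defined after randomisation. The protocol does not say how cleared patients count on day 9, 14, 30 or 60. The rule also asks for the two negatives within 24 hours, while scheduled swabs are three days apart, so a pair of scheduled swabs cannot meet it.

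**Step 4: Phase II days.** The synopsis has 6, 9 and 14; the body has 6 and 9. The two do not agree.

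**The case against.** The strongest objection is that the study flow chart in Appendix E, to which the procedures section refers, is not available here and may list the missing swabs. This stands as a limit. A reader might infer that none of the 182 Phase III patients would have a day-30 or day-60 swab, or that the endpoint cannot be computed at all. The documents support only that the written visit lists schedule none. If the chart does list a swab, the defect becomes a conflict between chart and text, and the day 30 versus day 60 contradiction remains.

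Two further readings go too far. First, one might say that the 24-hour condition can never be met. It can be read as a confirmatory repeat swab outside the routine grid, and the blood-test interval allows departures on clinical advice. The wording is unclear, but not impossible. Second, one might argue that almost everyone will be negative by day 60, so the endpoint is uninformative. The protocol gives no clearance rate at day 30 or 60, and its Rationale mentions prolonged viral persistence in patients with poor outcome. Nothing here rests on that argument.

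It is also fair to say that swab negativity is one of nine Phase III secondary outcomes in the body, and that Phase III starts only if Phase II meets its primary outcome. That limits the weight of the point but does not remove the contradiction.

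**Conclusion.** The point holds as an internal inconsistency that should be corrected. One stated Phase III secondary endpoint has two different days and no swab in the written visit list for either. Another, swab viral load, has a day-14 time point that no three-day grid can provide together with days 6 and 9. The Phase II viral-load days also differ between synopsis and body.

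This rests on the written visit text, with the flow chart unseen, and on reading the swab timing as the three-day blood-test interval. Swabs taken on clinical advice may exist, but they do not secure a measurement in every patient. The primary endpoint, its analysis and the sample size are not affected.

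**What to change.** - Use one day for swab negativity in both the synopsis and the Phase III secondary outcomes, and list the RT-PCR swab at that existing visit. If the sponsor wants no later swab, define the endpoint on the scheduled swabs up to day 14 instead.
- Name day 14 as a swab day in the days 1 to 14 assessments.
- Make the Phase II viral-load days the same in the synopsis and the body.
- State either that patients who stopped swabbing after two consecutive negatives are counted as negative, or below detection, on later endpoint days, or that they continue to be swabbed on those days. Apply the same rule in both arms.
- Reconcile the 24-hour condition with the three-day interval, saying whether a repeat swab outside the grid is intended.
- Check the Appendix E flow chart against the corrected text.

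The cost is amendment wording and at most one or two swabs per patient, at assessments already planned. If cleared patients are instead kept on swabbing, they would also have the endpoint-day swabs that they now skip.

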**Secondary endpoints**

Descriptive results will be presented as means  $\pm$  standard deviation (SD), medians with interquartile range (IQR), and percentages with 95% confidence intervals (CI). Chi-square or Fisher's exact test will be used to compare categorical variables. ANOVA and Student's t-test will be used for continuous variables unless they will be not normally distributed, in which case the Kruskal-Wallis or Mann-Whitney test will be used to compare continuous parameters. Kaplan-Meier product-limit estimates will be used to calculate time to different secondary endpoints. The log-rank test will be used to assess the difference between the survival curves among arms. Changes in some biomarkers respect to baseline values will be compared using paired Wilcoxon test. The association between primary outcome and transfusion dose of CCP expressed as ml/kg of the recipient body weight, adjusted for anti-Sars-CoV-2 neutralizing and ELISA antibody concentrations, will be investigated through regression analysis. All tests will be two-sided and a P value inferior to 0.05 will be regarded as significant.

**Analysis settings** Analysis will be carried out in the "intention to treat" set.

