- In-patient hospitalization or prolongation of existing hospitalization during the period of protocol-defined surveillance

- Results in congenital anomaly or birth defect
- Results in a persistent or significant disability/incapacity

Any other important medical event that may not result in one of the above outcomes, may be considered a serious adverse experience when, based upon appropriate medical judgment, the event may jeopardize the participant and may require medical or surgical intervention to prevent one of the outcomes listed above.

**AE/SAE relationship assignment.** For all collected AE's/SAE's, the clinician who examines and evaluates the subject will determine the adverse event's causality based on temporal relationship and his/her clinical judgment. The degree of certainty about causality will be graded using the categories below:

- **Definitely Related:** There is clear evidence to suggest a causal relationship, and other possible contributing factors can be ruled out. The clinical event, including an abnormal laboratory test result, occurs in a plausible time relationship to drug administration and cannot be explained by concurrent disease or other drugs or chemicals. The response to withdrawal of the drug (de-challenge) should be clinically plausible. The event must be pharmacologically or phenomenologically definitive, with use of a satisfactory rechallenge procedure if necessary.
- **Probably Related:** There is evidence to suggest a causal relationship, and the influence of other factors is unlikely. The clinical event, including an abnormal laboratory test result, occurs within a reasonable time sequence to administration of the drug, is unlikely to be attributed to concurrent disease or other drugs or chemicals, and follows a clinically reasonable response on withdrawal (de-challenge). Re-challenge information is not required to fulfill this definition.
- **Possibly Related:** There is some evidence to suggest a causal relationship (e.g., the event occurred within a reasonable time after administration of the trial medication). However, the influence of other factors may have contributed to the event (e.g., the subject's clinical condition, other concomitant events). Although an adverse drug event may rate only as "possibly related" soon after discovery, it can be flagged as requiring more information and later be upgraded to "probably related" or "definitely related", as appropriate.

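### Phase III adverse events are split by attribution to plasma, so a disease event misattributed to plasma leaves the non-plasma count in Arm A only; the between-arm comparison should use all adverse events

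*Protocol*

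**What the plan says.** Under Outcomes and Endpoints, the phase III secondary outcomes include three adverse-event rows:

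- "Total plasma related adverse event (Febrile reactions, TRALI, TACO, TTI) (day 60"
- "Total non-plasma related adverse events (day 60"
- "Severe adverse events (SAE) (day 60"

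Only the third is not split by cause. I read it as the serious adverse events defined in Appendix B. Phase II lists no adverse-event outcome.

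Under Interventions, Arm B is "Standard therapy with no CCP". There is no sham infusion. On masking, the protocol states: "The assignment to intervention will be unmasked to all trial participants (care providers, outcome assessors, and data analysts".

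Appendix B (AE/SAE relationship assignment) says that "the clinician who examines and evaluates the subject will determine the adverse" event's causality, "based on temporal relationship and his/her clinical judgment". It defines five grades of relatedness and does not say which of them count as plasma related. Appendix B also excludes grade 1 and 2 events from the adverse events, and has any adverse event recorded from consent to the final visit.

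Under Statistical methods, Secondary endpoints, chi-square or "Fisher's exact test will be used to compare categorical variables", two-sided at 0.05. No safety outcome is exempted.

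**The concern.** A between-arm comparison of safety needs an outcome that can be counted in the same way in both arms. Neither attribution-split row meets that condition. Arm B's plasma-related count is zero by definition, so every Arm B event falls in the non-plasma row. In Arm A an event can go to either row, and the choice is made by an unmasked clinician who relies partly on timing.

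COVID-19 pneumonia itself produces fever and respiratory worsening. Arm A has infusions on days 1 to 3 to which such an event can be linked in time, and Arm B has none. The same clinical event could therefore be removed from the non-plasma row in one arm and kept in the other.

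At stake is the reading of a secondary safety outcome. The protocol notes under Trial design that data on CCP in earlier disease are lacking, so whether recipients have more adverse events overall is a question that readers will ask.

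**Working it through.** **1. The plan's own figure.** The protocol gives no adverse-event rate or power. The relevant figure is the phase III arm size, 91. With 20% v 40%, two-sided alpha 0.05 and 80% power:

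- n = [1.96·√(2·0.3·0.7) + 0.8416·√(0.2·0.8 + 0.4·0.6)]² / 0.2² = 81.2, or 82 per arm.
- With continuity correction, (81.2/4)·[1 + √(1 + 4/(81.2·0.2))]² = 91 per arm, as stated.

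**2. Accounting for the rows.** For Arm A, let b be events not caused by plasma, r true plasma reactions, m disease events misattributed to plasma, and u plasma reactions graded as unrelated (0 ≤ u ≤ r).

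| | Arm A | Arm B |
|---|---|---|
| All-cause | b + r | b′ |
| Non-plasma row | b − m + u | b′ |
| Plasma row | r + m − u | 0 |

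- *Correct attribution (m = u = 0).* The non-plasma row compares b with b′ and is not biased. If 30% have a background event in both arms and a further 5% of Arm A have a true reaction (both assumed), the row shows 30% v 30%, risk ratio 1.00. All-cause shows 35% v 30%, risk ratio 1.17.
- *Disease events misattributed to plasma (m > 0).* Arm A's row falls by m. Nothing can leave Arm B's row, so the shift is toward CCP only.
- *Plasma reactions graded as unrelated (u > 0).* The row moves back toward the all-cause comparison. Because u ≤ r, it cannot pass it.

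**3. Illustration only.** The protocol gives neither the adverse-event rate nor the misattributed share, so both are assumed here. The calculation is an exact enumeration of the two-sided Fisher test at 0.05, with 91 per arm and the same true all-cause proportion in both arms. A share f of Arm A patients with an event has it labelled plasma related only.

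| True rate | f | Apparent risk ratio | False result for CCP | False result against CCP |
|---|---|---|---|---|
| 30% | 0 | 1.00 | 1.7% | 1.7% |
| 30% | 10% | 0.90 | 4.8% | 0.5% |
| 30% | 20% | 0.80 | 11.5% | 0.1% |
| 30% | 30% | 0.70 | 23.4% | 0.0% |
| 20% | 20% | 0.80 | 7.4% | 0.2% |
| 40% | 20% | 0.80 | 16.6% | 0.1% |

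This shows direction and sensitivity. It is not an estimate of what will happen, and f could be near zero.

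**4. The plasma-related row.** With Arm B fixed at 0 of 91, Fisher's test gives p = 0.059 for 5 of 91 and p = 0.029 for 6 of 91. Such a test asks only whether Arm A's labelled rate exceeds zero.

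**The case against.** Several points on the other side stand.

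- **The stated transfusion risks do not measure the bias.** The Benefit/Risk section gives 1 in 100 for allergic or febrile reaction and 1 in 100 for TACO. A reader might turn these into 1 − 0.99² = 2.0% of Arm A patients (rates per patient) or 1 − 0.99⁶ = 5.9% (rates per infusion, three infusions) and call that the tilt. The protocol does not support this. These are reactions caused by plasma, additional to disease events, and removing them correctly leaves the non-plasma comparison unbiased (step 2).
- **Many events are outside the problem.** Grade 1 and 2 events are not counted as adverse events. SAEs include prolonged hospitalization and important medical events, so most clinically important lung deterioration should appear in a row that is not split by cause.
- **It is not an efficacy signal.** A reader might infer a spurious efficacy finding. No efficacy outcome uses attribution: the primary outcome is a change on the WHO ordinal scale, and mortality is all-cause.
- **The test is not spelled out for these rows.** The statistical methods speak of categorical variables in general, and a total might be a count reported descriptively. That is fair, but the text sits under secondary endpoints, these rows are secondary endpoints, and nothing exempts them.
- **Nothing is lost.** A reader might infer that the all-cause question cannot be answered for non-serious events. It can: for event counts the two rows add up to the total, and the patient-level data are recorded. Patient proportions cannot be obtained by adding the rows, because one patient may appear in both.

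The bracketed list of reaction types could be read as sorting by type and not by judgment. That does not remove the problem, since a fever would still be classed differently in the two arms.

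**Conclusion.** The point holds as a limited one. As listed, the non-plasma row is open to a bias that can arise in Arm A only, and misattribution of disease events to plasma can move it only toward CCP. The plasma-related row has no meaningful comparator. This follows from the definitions, the absence of plasma in Arm B and the unmasked causality judgment.

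The size cannot be derived from the protocol, because it depends on the misattribution rate, and it could be small. It concerns phase III secondary safety outcomes, and mainly non-serious events of grade 3 or higher. The SAE row, mortality and the primary outcome are unaffected. It rests on two readings: that the general tests for categorical secondary endpoints apply to these rows, and that the SAE row is all-cause. The change is worth making because it is cheap and replaces a stated outcome that is open to bias. The point does not threaten the trial's main conclusion.

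**What to change.** In the phase III secondary outcomes:

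1. Make the between-arm adverse-event outcome all adverse events to day 60 regardless of attribution, expressed as the number of patients with at least one, by arm.
2. Keep the SAE comparison as it is.
3. Report plasma-related events for Arm A only, as a proportion with a 95% CI and no test against Arm B.

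The cost is protocol wording. Appendix B already has any adverse event recorded from consent to the final visit, so no new data are needed. The small downside is that disease-related events make the all-cause total less specific to plasma. The Arm A description of plasma-related events keeps that information.
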